With advances in cancer treatment over the decades, the survival time of older patients with cancer has been gradually extended, and the accompanying symptoms of chemobrain have gradually drawn increasing attention [5]. Recent data have shown that chemobrain-related stress could persist for a long-term period after a systemic therapy, which is particularly relevant to older patients with cancer [6]. These individuals report chemobrain symptoms of anxiety and depressive disorder, and the number of older patients with cancer will increase dramatically in the coming future. Although data on cognitive impairment onset after chemotherapy are lacking for older patients with cancer in China, clinical practitioners have paid constant attention to the health of their constituents, given their propensity for worse physical and mental health outcomes related to chemotherapy [7]. Data suggest that up to two-thirds of older patients with cancer develop chemobrain during or after chemotherapy [8]. Most of these patients experience cognitive impairments for months, but 10%-20% of these individuals experience persistent chemobrain-related stress even after many years of completing chemotherapy. In recent years, the incidence rate of cancer in senile patients has been rising in China [9]. The problem of chemotherapy-induced cognitive dysfunction is becoming increasingly common, and there are growing concerns that chemobrain could become a threat. Therefore, it is crucial to explore an intervention that can effectively prevent and treat chemotherapy-induced cognitive impairment in older patients with tumors.

Pre-existing studies [10] have shown that some neuroprotective factors such as methylphenidate and modafinil are effective for treating chemotherapy-related cognitive impairment; however, most clinical trials on interventions for chemobrain report less access to control groups and less treatment engagement. Combo acupoint stimulation therapy is a new technique based on the theory of traditional Chinese medicine and modern biological principles. With the help of invasive or noninvasive interventions, different stimuli or drug intakes would be administered at acupuncture points, meridians, or related specific body surface sites [11].

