#### Sample Size Estimation

A total of 168 older patients with cancer will be recruited, of which 84 will be in the experimental group (EA) and 84 will be in the control group. Sample size calculation:

n = [p1 (1 – p1) + p2 (1 – p2)]/(p1 – p2)] × Cp.power

Cp refers to the process capability index. In the 2-sided test, Cp.power = 10.5 when *P*<.05 is met. n is the number of patients to be recruited in each group, p1 and p2 represent the incidence in each group, and a mean difference with 95% level of significance (α) and 80% power (1 – β) is set. In older patients with cancer, the incidence of chemobrain after chemotherapy is 30%, and the reduction of chemobrain could be 10%-20% with acupuncture intervention. The sample size for each group is 84 participants, considering a 20% dropout. Therefore, the overall target sample size of 168 will be included.

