## Discussion

Patients with cancer may have concerns of psychiatric and digestive symptoms while undergoing or just after having recently undergone chemotherapy [3]. The most common clinical manifestations are fatigue, nausea, vomiting, dry mouth, anxiety, depression, and insomnia. More seriously, cognitive impairments with a range of neurocognitive symptoms occur frequently, including visual and verbal memory impairment, forgetfulness, difficulty concentrating, learning difficulties, and organizational and coordination dysfunction [3,4]. Since the 1980s, researchers have been studying chemotherapy-induced cognitive impairment and have given several definitions to this condition, such as postchemotherapy cognitive impairment and chemotherapy-induced cognitive dysfunction. Recently, this condition was termed as chemobrain [3-5].

Chemobrain is a frequent side effect experienced by an increasing number of older patients with cancer, and it has significantly impacted their QoL [4]. Chemobrain can be described as cognitive symptoms reported by patients with cancer in self-reported questionnaires or as cognitive changes evaluated by formal neuropsychological tests [5]. Older patients with cancer will experience cognitive impairment due to chemoradiotherapy, which will lead to a series of neurocognitive symptoms called chemobrain. Older populations have been disproportionately affected by chemobrain and have heightened negative mental health outcomes after cytotoxic chemical drug therapy [3,5,7].

According to available literature [3,14], more than 75% of patients with cancer experience cognitive impairment while undergoing chemotherapy or just after completing chemotherapy, with 15%-30% of these patients experiencing persistent symptoms for up to decades. The prevalence of postchemotherapy cognitive impairment is as high as 50%-75% among older cancer survivors [33]. In some circumstances, the cognitive impairment can be lifelong, affecting the patient’s mood, relationships, QoL, career, social activity, and family life. Considering the increasing incidence of cancer, chemobrain is quite complicated, increasingly important, and has far-reaching consequences. As the incidence of cancer survivors rises, the adverse effects of chemobrain will become more frequent, thus necessitating the need to effectively prevent and treat chemobrain.

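### The sample-size paragraph contradicts itself (80% power beside a 90% constant; 84 per arm not given by its formula), and 168 patients give 80% power for incidence only near the top of the stated effect range

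*Protocol article*

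**What the plan says.** All the sizing is in one paragraph of the protocol article, Sample Size Estimation.

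- Formula: "n = [p1 (1 – p1) + p2 (1 – p2)]/(p1 – p2)] × Cp.power". The brackets do not balance.
- Multiplier: "In the 2-sided test, Cp.power = 10.5 when *P*<.05 is met". The text calls Cp a process capability index.
- Error rates: "a mean difference with 95% level of significance (α) and 80% power".
- Effect: "the incidence of chemobrain after chemotherapy is 30%, and the reduction of chemobrain could be 10%-20% with acupuncture intervention". No single value within the range is chosen.
- Result: "The sample size for each group is 84 participants, considering a 20% dropout", so 168 in total.

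Elsewhere, the Introduction says that "up to two-thirds of older patients with cancer develop chemobrain during or after chemotherapy", and the Discussion says: "The prevalence of postchemotherapy cognitive impairment is as high as 50%-75% among older cancer survivors". The Statistical Analyses section plans a Kaplan-Meier comparison of cumulative incidence over 8 weeks and tests at P<.05. The abstract names the MoCA score as the primary outcome.

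**The concern.** The paragraph gives its formula, constant, power, inputs and result, so it can be checked, and the parts do not agree. The power label and the constant belong to different designs. The result does not come out of the formula. A reader also cannot tell whether 84 was meant for a 10-point reduction, a 20-point reduction or something between.

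At stake is how a null incidence result would be read. It would be taken as coming from a trial with 80% power. At the smaller reduction that the paragraph itself allows, the chance of detecting the effect is about one in four.

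**Working it through.** **Inputs (all from Sample Size Estimation).** p1 = 0.30. An absolute reduction of 10 to 20 points gives p2 = 0.20 to 0.10. Test two-sided at 5%, stated power 80%, multiplier 10.5, dropout 20%, 84 per arm.

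**1. The constant.** For two-sided 5%, C = (1.960 + z)².
- 80% power: (1.960 + 0.842)² = 7.85
- 90% power: (1.960 + 1.282)² = 10.51

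The printed 10.5 is therefore the 90% value.

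**2. Trying to reproduce 84.** Let V = p1(1 − p1) + p2(1 − p2) and d = p1 − p2. Each n is rounded up, divided by 0.8 for dropout and rounded up again.

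| p1 vs p2 | V | As printed: V/d × 10.5 | Squared: V/d² × 10.5 (90%) | Squared: V/d² × 7.85 (80%) |
|---|---|---|---|---|
| 30% vs 20% | 0.3700 | 39 → 49 | 389 → 487 | 291 → 364 |
| 30% vs 15% | 0.3375 | 24 → 30 | 158 → 198 | 118 → 148 |
| 30% vs 10% | 0.3000 | 16 → 20 | 79 → 99 | 59 → 74 |

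None of these rows gives 84, before or after dropout.

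If 10%-20% is read as a relative reduction, p2 is 0.27 to 0.24. At 0.24 the printed formula gives 0.3924/0.06 × 10.5 = 68.7, so 69, then 83 (× 1.2) or 87 (÷ 0.8). That is near 84 but not equal to it. With the difference squared and 80% power, the same scenario needs 0.3924/0.0036 × 7.85 = 856 evaluable, or 856/0.8 = 1,070 randomised per arm.

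**3. Power that 84 per arm gives for incidence.** Pooled-variance z test, power = Φ{[d − 1.96 √(2p̄(1 − p̄)/n)] / √(V/n)}, where p̄ is the mean of p1 and p2. After 20% dropout, n = 84 × 0.8 = 67.

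- 30% vs 10%, n = 67: (0.20 − 1.96 × 0.0691)/0.0669 = 0.965, power 83%
- 30% vs 15%, n = 67: (0.15 − 1.96 × 0.0721)/0.0710 = 0.121, power 55%
- 30% vs 20%, n = 67: (0.10 − 1.96 × 0.0748)/0.0743 = −0.627, power 27%

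| Reduction | 67 per arm | 84 per arm (no dropout) |
|---|---|---|
| 20 points | 83% | 91% |
| 15 points | 55% | 65% |
| 10 points | 27% | 32% |
| Smallest reduction with 80% power | 19.4 points | 17.6 points |

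On the relative reading, power is about 6% at 30% vs 27% and 12% to 14% at 30% vs 24%.

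**4. Check against the planned analysis.** A log-rank calculation (Schoenfeld, proportional hazards) with 67 per arm gives 27%, 58% and 88% at 10, 15 and 20 points, with 80% reached at 18.4 points. The picture is the same.

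**5. MoCA as a continuous outcome.** With 67 per arm and a two-sided 5% t test, 80% power needs a standardised difference of about 0.49 (normal approximation √(2 × 7.85/67) = 0.484). The article gives no MoCA difference or SD to compare this with.

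**The case against.** Several points can be said for the plan.

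- **The square may simply be lost.** The bracket is unmatched at exactly that place, so a superscript could have dropped out in typesetting or in reading the PDF. This stands. The unsquared form should not be treated as a proven error by the authors, but the squared form does not give 84 either.
- **A route to 84 exists.** A reader might infer that no calculation reaches 84. A Freedman log-rank calculation at 30% vs 10%, two-sided 5% and 80% power has a hazard ratio of 0.295 and needs 26.5 events, or 26.5/0.40 = 66.3 per arm. Rounded to 67, that is 67/0.8 = 83.75, so 84. It uses the stated numbers and suits the Kaplan-Meier comparison, but it is not the printed formula, and nothing shows that it was used.
- **The slips did not cause the low power.** A reader might link the two. Using 10.5 in place of 7.85 makes n larger, and the printed formula gives far fewer than 84 on the absolute reading. The two issues are separate.
- **The paragraph does not promise 80% power across the whole range.** This is true, and at 30% vs 10% the trial has it. What remains is that the design value is not named.
- **The trial as a whole is not shown to be underpowered.** The figures concern incidence only. Power for MoCA scores in the mixed model cannot be computed from the article.
- **The 30% is not strictly contradicted.** The Introduction gives an upper bound during or after chemotherapy, and the Discussion a prevalence among survivors. These may be different measures, so the 30% needs a justification and cannot be called wrong.
- **The alpha wording is a slip.** P<.05 is stated in the same section and again in Statistical Analyses.

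**Conclusion.** The point holds in this form. The paragraph is wrong as written: its power and its constant disagree, its alpha is misstated, its multiplier is misnamed, its design effect is not named, and its formula does not give 84 with or without the square.

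Separately, 84 randomised per arm give 80% power for the incidence comparison only for absolute reductions of at least about 19 points (about 18 with no dropout). Between 76% ((17.6 − 10)/10) and 94% ((19.4 − 10)/10) of the 10-20 point range lies below 80%. At 10 points power is 27% to 32%.

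This assumes a 30% control incidence, absolute reductions, a two-sided 5% test and a simple comparison of proportions. The log-rank version agrees, and a relative reading is much worse. It says nothing about power for MoCA scores.

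**What to change.** Keep 168 patients and rewrite the paragraph:

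1. Print the formula with (p1 − p2) squared and balanced brackets.
2. Pair 7.85 with 80% power, or 10.5 with 90%, and drop the process-capability label.
3. State alpha as 5%, two-sided.
4. Apply dropout as n/0.8.
5. Name the design effect and say whether it is absolute or relative. If 84 came from another method, such as a log-rank calculation, print that method.
6. State that 84 randomised (67 evaluable) per arm give about 80% power only for an absolute reduction of about 19-20 points from 30%, and about 27% for 10 points.
7. If the MoCA score is the primary outcome, base the statement on it instead: about 0.49 standard deviations detectable with 67 per arm.
8. Justify the 30% incidence against the higher figures in the Introduction and Discussion, saying which measure and time window each describes.

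The cost is one paragraph and a less favourable power statement, with no extra patients. Restating the figures does not raise the power at small reductions; it lets a null result be read correctly.

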### Statistical Analyses

Cognitive impairment is defined as those with SD>1.5 in the mean scores of MoCA and the QLQ-C30 at baseline for all participants at different timepoints. A time-series test in the Kaplan-Meier survival analysis will be used to compare the incidence of cognitive deficits accumulated after 8 weeks of acupuncture intervention between the 2 groups. Linear mixed-effects modeling will be used to compare participants’ cognitive impairment, fatigue, and depression at baseline, during, and after acupuncture intervention, where only those who have completed at least one assessment at baseline and during treatment will be compared. This model will use time and group as categorical fixed factors and random intercepts and use random intercepts in conjunction with a measurement covariance matrix. Participants’ age, chemotherapeutic drug dosage, fatigue at baseline, depression, and additional treatments will be considered as covariates in the statistical analyses. A 2-sided *t* test will be used to compare the covariates at each timepoint between the 2 groups. The chi-square test will be used for qualitative information and the *t* test will be used for continuous information at baseline. Statistical significance will be considered at *P*<.05. The study data used will be statistically analyzed using SPSS software (IBM Corp) under the supervision of a statistician. To ensure the privacy of the patients, all relevant study data and personal data will be kept in a locked file cabinet. Electronic data will be stored on an encrypted computer and will not be stored on any external storage device. Each participant will be assigned his or her own ID in the study record, which will be used in lieu of his or her name and personal identifying information. Clinical data from the study will be kept in a separate file from the participant’s personal data. The principal investigator will be responsible for all the clinical trial data. During and after the clinical trial, the principal investigator, researchers, and the ethical review committee have the right to view the study data. Participants will have the right to access their personal data and the results of the study. All study data will be stored for a minimum of 3 years after the completion of the trial, after which they will be destroyed in accordance with the rules of the ethics review committee.

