### Assessments

In this study, therapeutic efficiency will be assessed in terms of the following aspects: cognitive performance, fatigue, QoL, and chemotherapy-induced side effects. The primary outcome of this study is to verify whether EA is therapeutically useful for preventing chemobrain and alleviating the related symptoms and the safety of intervention. Cognitive performance will be assessed using MoCA + FACT-Cog. The secondary outcomes are as follows: QoL will be measured using EORTC QLQ-C30, fatigue will be assessed using the FACIT-Fatigue scale, and the manifestation of chemotherapy-induced side effects will be assessed using the Chemotherapy Symptom Rating Scale FAACT + FACT-BRM. All assessment scales will be evaluated by previously trained researchers at the following timepoints (see Figure 2): baseline (T0), midpoint of main treatment (T1-T3) once every 2 weeks, and end of the 8-week main treatment (T4) (a total of 5 timepoints). We will also keep a record of all the shedding cases. This study is a multidisciplinary clinical trial (across oncology and Chinese medicine disciplines) on the role of Chinese acupuncture as therapy for chemotherapy-induced cognitive impairment in older patients with cancer. If successful, findings from this study might have beneﬁts in reducing chemotherapy-induced working memory impairment. Data from this study may be used to support an implementation and dissemination trial of Chinese EA in real-world behavioral health and social service settings.

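### The cognitive-impairment event has no direction, leaves both-or-either open, counts a quality-of-life score as cognition, and is not linked to the 30% planning incidence

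*Protocol article*

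**What the plan says.** The Statistical Analyses section gives the only definition of the event: "Cognitive impairment is defined as those with SD>1.5 in the mean scores of MoCA and the QLQ-C30 at baseline for all participants". The sentence goes on to apply this at different timepoints. The next sentence plans a Kaplan-Meier type analysis to "compare the incidence of cognitive deficits accumulated after 8 weeks of acupuncture intervention between the 2 groups".

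The Assessments section assigns the instruments differently. On cognition it says "Cognitive performance will be assessed using MoCA + FACT-Cog"; among the secondary outcomes it says "QoL will be measured using EORTC QLQ-C30". Study Procedures makes the same assignment. There are five assessments: baseline and four later visits, the last at week 8.

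The Sample Size Estimation section plans on an incidence. It says that "the incidence of chemobrain after chemotherapy is 30" per cent and that "the reduction of chemobrain could be 10%-20% with acupuncture intervention". It does not refer to the 1.5 SD rule.

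**The concern.** An event rule has to tell the analyst which patients have the event. This one leaves three choices open and makes one that conflicts with the rest of the article.

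- **Direction.** Nothing says that the deviation must be downward, so read literally an unusually good score qualifies. The rest of the article does not settle it. Specific Aims and Hypotheses predicts greater reductions in MoCA with electroacupuncture, whereas the Introduction treats a better MoCA score as the benefit.
- **Both or either.** The rule joins MoCA and QLQ-C30 with a bare conjunction. It can mean that both must be past the line or that either is enough.
- **Baseline cases.** No rule covers patients who already meet the definition before treatment, although the comparison is of incidence.
- **Instrument.** A measure assigned to quality of life enters the cognitive event, and FACT-Cog, assigned to cognition, does not.

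The sample size rests on a comparison of two incidences, and this is the only place where the event is defined. If the choices stay open, they can be made after the data are seen, and the event rate changes several-fold with them. Crossings due to test variation also occur in both arms alike and dilute any difference.

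**Working it through.** **Inputs from the article:** cut-off 1.5 SD of the baseline distribution; four post-baseline visits; planning incidence 30%; reduction 10-20%.

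**Assumptions, because the article gives no figures:** normal scores; each instrument treated as one score; correlation between visits r = 0.5 to 0.9, equal for all pairs of visits; correlation between the two instruments 0 to 0.5.

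**Step 1. Share past the line at baseline, by reading.** With Φ the standard normal distribution function:
- MoCA alone, low side: Φ(-1.5) = 6.7%. Either direction: 2 × 6.7% = 13.4%.
- Both scores low: 0.0668² = 0.4% at correlation 0, and 1.8% at 0.5.
- Either score low: 2 × 6.68% - 0.45% = 12.9% at correlation 0, and 11.5% at 0.5.
- Either score, either direction: 24.9% at correlation 0, and 23.0% at 0.5.

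The same sentence thus supports a baseline share anywhere from 0.4% to about 25%.

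**Step 2. Crossings from test variation alone.** Take one score, a stable true level and no change. Write a visit score as √r·U + √(1-r)·e, with U and e standard normal. Given U, a visit is not low with probability p(U) = Φ((1.5 + √r·U)/√(1-r)). Among patients not low at baseline (93.32%), the share low at one or more of four later visits is

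1 - E[p(U)⁵] / 0.9332.

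For either direction, p(U) becomes the probability of lying within ±1.5 and the divisor becomes 0.8664.

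| r | E[p⁵], low side | crossing, low side | E[p⁵], either direction | crossing, either direction |
|---|---|---|---|---|
| 0.5 | 0.7884 | 15.5% | 0.5800 | 33.1% |
| 0.6 | 0.8074 | 13.5% | 0.6155 | 29.0% |
| 0.7 | 0.8278 | 11.3% | 0.6557 | 24.3% |
| 0.8 | 0.8506 | 8.9% | 0.7012 | 19.1% |
| 0.9 | 0.8779 | 5.9% | 0.7559 | 12.8% |

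Requiring two consecutive low visits reduces the low-side figures to about 2-3%.

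**Step 3. What such crossings do to the comparison (illustration).** Take the larger planned contrast, 30% against 10%. Let a share f of the remaining patients in each arm cross by chance, independently of true events. The arms become 0.30 + 0.70f and 0.10 + 0.90f, so the difference is 0.20 × (1 - f). For f = 0.059 it is 0.188, for f = 0.155 it is 0.169, and for f = 0.33 it is 0.134.

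**Step 4. Relation to the 30%.** The 30% is stated as an incidence after chemotherapy; Step 1 concerns the baseline share only. For 30% of patients to be low at one later visit, the mean must fall by z(0.30) + 1.5 = -0.524 + 1.5 = 0.98 SD. For 30% cumulative incidence over four visits among patients not low at baseline, the fall needed is 0.41 SD (r = 0.5) to 0.79 SD (r = 0.9). The rate under the definition can therefore reach 30%. Whether it does depends on direction, both-or-either, baseline cases and reliability, none of which the article fixes.

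How the 84 per group was obtained from the 30% is a separate question and is not used here.

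**The case against.** The strongest reply has four parts.

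**The cohort's own baseline is a reasonable reference.** The inclusion criteria do not require chemobrain and admit patients about to start chemotherapy, and prevention is among the aims. For new decline in such patients, a line set on baseline scores is defensible. This stands, and the fix keeps it. A reader might infer from the Abstract, which describes enrolled patients as having confirmed chemobrain, that the rule would label about 93% of true cases unimpaired. The documents do not support that as a finding. It needs normality and the Abstract's description, which the Inclusion and Exclusion Criteria do not match; that mismatch is a different point.

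**The 30% is not contradicted.** This also stands. It is tempting to say that a 1.5 SD cut-off, flagging about 7%, cannot produce a 30% incidence. That confuses a baseline share with an incidence accumulated after chemotherapy, and Step 4 shows that 30% is reachable. Likewise, 30% against 10% corresponds to 0.76 SD between arms on normal scores of equal variance at any cut-off, so it says nothing against this one.

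**The article does not say that a single visit past the line is an event, or that the QLQ-C30 must qualify.** Correct: both are readings of a rule that is silent. Confirmation rules may be left to a fuller document. The noise figures apply if one visit counts.

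**The noise range rests on assumed correlations.** It does, and at r = 0.9 the low-side figure is only 5.9%.

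None of this answers the missing direction, the both-or-either ambiguity or the use of a quality-of-life score. These lie in a rule that the article states, and the instrument conflict is between its own sections.

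**Conclusion.** The event rule is wrong as written. Followed literally, an unusually good score or a change in quality of life could count as a cognitive event, and patients past the line at baseline are not set aside. These points rest on the text alone.

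The sizes rest on assumptions: normal scores, equal visit correlations of 0.5 to 0.9, and one visit counting as an event. Under them, 6-16% of patients unimpaired at baseline would cross the low line with no true change, and 13-33% would cross in either direction. The larger planned difference of 20 percentage points would shrink to about 17-19 points on the low side and to about 13 points at the worst either-direction figure.

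On the planning rate, the conclusion is limited: the 30% has not been derived from this definition or reconciled with it. It has not been shown to be unattainable.

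**What to change.** In Statistical Analyses, define the event as a MoCA score more than 1.5 baseline SD below the baseline mean, both taken from the two arms pooled, among patients not below that line at baseline. Remove the QLQ-C30 from the definition and report it as a quality-of-life outcome, as Assessments already does. In Sample Size Estimation, state that the 30% was not obtained under this definition.

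The cost is wording only: MoCA is already collected at all five timepoints. Under normality, about 6.7% of 168, or 11 patients, would start below the line and leave this one analysis. They are identified from baseline data, so the randomized comparison is kept. The line remains relative to the trial's own sample, and the low-side crossings of Step 2 remain if one visit counts.

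An event confirmed at the next visit can be added as a sensitivity analysis. It cuts noise crossings to about 2-3%, at the price of fewer events, and a first event at T4 cannot be confirmed.

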### Questionnaires/Instruments

#### MoCA Self-Reported Questionnaire

The MoCA self-reported questionnaire is the main method used for assessing cognitive function. To objectively measure the cognitive impairment patterns of the participants, MoCA, a sensitive, time-sparing tool with high diagnostic validity, will be used to measure the degree of chemobrain. We evaluate the utility of MoCA as a chemobrain screening test for older patients with cancer who are undergoing or about to receive chemotherapy. Participants will be instructed to self-report their cognitive functions through MoCA for 5 consecutive timepoints from baseline to the end of the 8-week treatment. Statistical software will be used to analyze participants’ cognitive function information recorded in case report forms.

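### The incidence comparison that sizes the trial uses an unadjusted Kaplan-Meier test and leaves out baseline MoCA: valid, but probably inefficient

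*Protocol article*

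**What the plan says.** The Sample Size Estimation section compares two incidences: "the incidence of chemobrain after chemotherapy is 30%, and the reduction of chemobrain could be 10%-20% with acupuncture intervention". It arrives at 84 per group: "The sample size for each group is 84 participants, considering a 20% dropout".

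The Statistical Analyses section assigns that comparison to a Kaplan-Meier method: "A time-series test in the Kaplan-Meier survival analysis will be used to compare the incidence of cognitive deficits accumulated after 8 weeks". The test is evidently of log-rank type, and no covariate is named for it. Cognitive impairment is defined there by a 1.5 SD criterion on MoCA and QLQ-C30 scores, with reference to baseline.

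After describing a separate linear mixed model, the same section says that "age, chemotherapeutic drug dosage, fatigue at baseline, depression, and additional treatments will be considered as covariates in the statistical analyses". Baseline fatigue is on the list; baseline MoCA is not.

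MoCA is available at baseline for every patient. The MoCA section has participants complete "MoCA for 5 consecutive timepoints from baseline to the end of the 8-week treatment", and Study Procedures places the baseline assessment before randomisation.

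**The concern.** If the event is a score crossing a cut-off, a patient's own starting score should be one of the best predictors of the event. The planned test treats a patient who starts just above the cut-off and one who starts far above it as having the same risk. The variation that baseline MoCA could explain stays in the comparison as noise.

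The listed covariates do not help. Even if the covariate sentence is meant to cover every analysis, a Kaplan-Meier curve test cannot take age or dosage as continuous terms, and the most relevant baseline score is absent from the list.

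What is at stake is power for the quantity that sets the trial size, using data that will be collected anyway. The point concerns the incidence comparison only. The mixed model of scores already includes baseline as a timepoint.

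**Working it through.** **1. The plan's own figure.** Inputs from Sample Size Estimation: p1 = 0.30; an absolute reduction of 0.10 to 0.20 (absolute is assumed, as the text does not say); "95% level of significance (α) and 80% power", read as α = 0.05; multiplier 10.5; 20% dropout.

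- The multiplier for two-sided 0.05 is (1.960 + 0.842)² = 7.85 at 80% power and (1.960 + 1.282)² = 10.5 at 90% power. The plan states 80% and uses 10.5.
- With the denominator squared, 30% v 20% gives (0.21 + 0.16)/0.01 × 10.5 = 388.5 per arm, and 30% v 10% gives (0.21 + 0.09)/0.04 × 10.5 = 78.8, or 78.75/0.8 = 98.4 with dropout.
- As printed, with the denominator not squared, the results are 38.9 and 15.8 per arm.
- A standard two-proportion calculation at 80% power gives 294 per arm (368 with dropout) for 30% v 20%, and 62 (78 with dropout) for 30% v 10%.

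None of these gives 84. The check below therefore takes 84 as fixed, with 84 × 0.8 ≈ 67 evaluable per arm.

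**2. Unadjusted power at 67 per arm.** Formula: power = Φ(z − 1.96), where z = (p1 − p2)/√{[p1(1 − p1) + p2(1 − p2)]/67}.

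- 30% v 10%: z = 0.20/√(0.30/67) = 2.99; power 85%.
- 30% v 15%: z = 0.15/√(0.3375/67) = 2.11; power 56%.
- 30% v 20%: z = 0.10/√(0.37/67) = 1.35; power 27%.

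The 15% case is a midpoint chosen here; the plan gives only the range.

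**3. Power with baseline MoCA in the model.** Assumptions that are not in the protocol:

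- normal scores at baseline and four visits, with equal correlation between any two visits;
- an event on MoCA alone, at 1.5 SD below the baseline mean;
- patients already below that cut-off at baseline excluded, with 67 per arm kept;
- arm means set to give the stated 8-week incidences.

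The comparison is the log-rank test against the group term (Wald test) of a complementary log-log discrete-time model with visit, group and baseline score. Results from 3,000 simulated trials per cell (the 0.3 row comes from 1,500):

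| Correlation | 30% v 10% | 30% v 15% | 30% v 20% |
|---|---|---|---|
| 0.3 | gain about 0–1 point | 55% → 56% | gain about 0–1 point |
| 0.5 | 85% → 88% | 55% → 59% | 29% → 31% |
| 0.6 | 85% → 90% | 55% → 63% | 28% → 32% |
| 0.7 | 85% → 93% | 58% → 71% | 29% → 36% |

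Separate runs of the same design agreed to within simulation error. At 30% v 15%, for example, they gave 59% → 64% at 0.5, 56% → 65% at 0.6 and 56% → 69% at 0.7. Over all runs the gain is about 0–1, 2–5, 4–9 and 6–13 points at the four correlations.

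**4. Type I error** (30% in both arms). The adjusted Wald test ran at about 5–6%. The highest single estimate was 6.6%, at correlation 0.7, with simulation error of about 0.5 point. The log-rank test gave 5.1–5.5%.

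**5. Other constructions.**

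- With the cut-off simply placed to give the stated incidence, gains were larger: about 2–3 points at 0.3, 6–7 at 0.5 and 12–21 at 0.7.
- With the event read as a 1.5 SD fall from the patient's own baseline, 30% v 15% moved from 55% to 62% at 0.5, to 60% at 0.6 and to 58% at 0.7. Adjustment still helps, through regression to the mean, but the gain shrinks as the correlation rises.

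**The case against.** Several objections have force.

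**The unadjusted test is valid.** A reader might infer that leaving out baseline MoCA biases the comparison. It does not: in a randomised trial, chance imbalance is already covered by the type I error of the log-rank test.

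**The gain is not established.** A reader might infer that the trial is certain to lose a known amount of power. The protocol gives no correlation, and at 0.5 or below the gain is about 5 points at most in the main set-up. Part of a gain that small could reflect the slightly liberal Wald test.

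**A shortcut calculation overstates it.** Taking a correlation of 0.5 between baseline MoCA and the event itself, and shrinking the variance by 1 − 0.5² = 0.75, lifts power at 30% v 15% from 56% to about 68%. This should not be used. In the simulated design a between-visit correlation of 0.5 gives a baseline-to-event correlation of only about 0.38 in the 30% arm and 0.31 in the 15% arm. Even a between-visit correlation of 0.7 gives about 0.52 and 0.41.

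**The simulated event is not exactly the documented one.** The definition also names QLQ-C30, and its wording allows more than one reading. No rule says who is at risk of a new event. The Abstract and Study Design describe recruiting patients who are already impaired, while the Abstract's Conclusions also speak of prevention. These points limit the precision of the figures. They do not reverse the direction, since both event definitions simulated showed a gain.

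**Other analyses and the unseen analysis plan.** The Abstract names MoCA scores as the primary outcome, and the Kaplan-Meier comparison is not labelled primary. Covariate detail is often left to the analysis plan. But the article does fix both a test and a covariate list for this comparison, and the mixed model does not test incidence. As stated, the incidence test remains unadjusted.

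**Conclusion.** The point holds as one of efficiency. The comparison that sets the sample size uses a test that cannot take the baseline value of a scale defining its event, and that value is missing from the covariate list as well. The likely benefit of adjusting ranges from negligible at a correlation of 0.3 to about 6–13 points of power at 0.7. These figures are conditional on an assumed correlation, a MoCA-only event and exclusion of patients past the cut-off at baseline.

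Adjustment is worth making because it is nearly free, but it does not rescue the trial. At 30% v 20%, power stays at 36% or below in the main simulations, against the 80% stated. The sample size needs separate correction.

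**What to change.** - Keep the Kaplan-Meier curves as the display and the unadjusted log-rank test as a sensitivity analysis.
- Take the treatment test from the group term of a discrete-time proportional-hazards model over the four follow-up visits (binary regression, complementary log-log link) with visit, group, continuous baseline MoCA and age. Add baseline QLQ-C30 if it stays in the event definition.
- Report the standardised 8-week risk difference with its confidence interval.
- Add baseline MoCA to the covariate list in Statistical Analyses.
- State the event definition and the at-risk rule unambiguously first, because the model cannot be fully specified without them.

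**Cost.** Analysis wording only. The data are already scheduled at baseline, and SPSS, the named software, can fit the model. There are two small downsides. The hazard ratio becomes conditional on baseline and will differ somewhat from the unadjusted one, which is why the standardised risk difference is reported too. Type I error of the Wald test may run slightly above 5% (about 5–6%); a likelihood-ratio or score test could be considered instead.
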